## Abstract

**Background::**

Adverse Childhood experiences (ACEs) disproportionately affect minoritized and low-income youth. Those with four or more ACEs are particularly vulnerable to chronic, unpredictable stress, which shapes their stress perception and response. Higher exposure to ACEs is associated with an increased risk of self-dysregulation, early initiation of alcohol and substance use, and cardiometabolic issues, including disruptions in heart rate variability, sleep disturbances, weight dysregulation, and elevated blood pressure. While some evidence-based family interventions aimed at preventing traumatic stress exist, research explicitly focused on interventions using psychoeducation incorporating biofeedback remains limited. The purpose of this paper is to describe the study protocol for a randomized controlled trial with adversity-impacted adolescents ages 11 to 14 and their caregivers. The THRIVE Study examines the efficacy of the Garnering Resilience in Traumatized youth and families (GRIT) intervention, a psychoeducational coaching program focused on building buffering protective factors, compared to an attention control group receiving a grade-specific Digital Literacy Intervention in delaying the initiation of alcohol and cannabis use.

**Methods::**

Adolescent-caregiver dyads (n= 210) are recruited to participate in six 1-hour intervention sessions conducted over 8 weeks via Zoom, facilitated by an intervention-specific community health worker (CHW). In-person assessments are conducted at specific time points: pre-intervention, post-intervention, 6-month follow-up, and 12-month follow-up. During these assessments, heart rate variability using the emWave Pro Plus and survey data are collected using REDCap to evaluate emotional and cognitive function, and behavioral outcomes (e.g., sleep disturbances and substance use). Additionally, participants complete a booster session and online surveys at 6-months post intervention.

**Discussion::**

The THRIVE Study evaluates a psychoeducational health coaching intervention that incorporates biofeedback. The findings from this RCT have the potential to build buffering protective factors in adversity-impacted adolescents and their caregivers, reducing long-term health inequities among minoritized and underserved populations.

**Trial registration::**

trial registration name: ClinicalTrials.gov, trial registration number: NCT06821035, registration on date: July 18th, 2025

## Introduction

Adverse Childhood Experiences (ACEs), which include childhood maltreatment, family dysfunction (1–4), and other forms of trauma, constitute a serious public health issue in the United States, disproportionately affecting minority and impoverished populations (5–7). Approximately 60% of adults (8,9) and nearly half of adolescents in the U.S. report exposure to at least one ACE, and those exposed to four or more ACEs (heretofore referred to as adversity-impacted) face greater risks of emotional dysregulation and challenges in self-regulation (9–11). This heightened vulnerability often leads to maladaptive coping mechanisms, including the early initiation of alcohol and substance use (12).

The physiological consequences of ACEs are profound, as toxic stress can disrupt the body’s autonomic nervous system, leading to a chronic state of dysregulation (13,14). One way to measure and address this dysregulation is through vagally-mediated heart rate variability (HRV), which refers to the variation in time intervals between heartbeats and is widely accepted as a biomarker of autonomic function and self-regulation (15–17). HRV reflects the body’s ability to adapt to stress and manage emotional responses, making it a key indicator of how well individuals can regulate their physiological and emotional states (18). Lower HRV has been linked to increased stress, emotional dysregulation, and greater vulnerability to substance use (19–22). Given the malleability of HRV and its established association with stress, substance use, and mental health challenges, HRV biofeedback (HRV-BF) offers a promising approach to enhance self-regulation in adversity-impacted youth. HRV-BF, using tools like the Inner Balance^™^ Trainer, leverages techniques such as slow-paced breathing to strengthen vagal tone, reduce stress, and promote emotional resilience (15–17,23–25).

Building on these principles, the Garnering Resilience in Traumatized Youth and Families (GRIT) program was developed as a community health worker-led health coaching intervention to integrate HRV-BF with psychosocial support. The conceptual framework of GRIT is rooted in the Shift and Persist model, which posits that children who experience chronic, unpredictable stress develop altered perceptions of and responses to stress (26,27). However, specific strategies, referred to as Shift and Persist, can mitigate these effects. These strategies, facilitated through a community health worker (CHW) serving as a positive role model, teach adolescents to self-regulate their emotions through cognitive reappraisals (e.g., HearthMath techniques), build trust via co-regulated relationships, and adopt a future-oriented mindset by setting goals, building healthy habits, and clarifying values.

The GRIT program also aligns with the California Surgeon General’s guidelines for mitigating toxic stress by promoting key factors, including nurturing relationships, mindfulness, and healthy habits (28). These theoretical foundations shape GRIT’s comprehensive approach to facilitating self-regulation in adolescent-caregiver dyads, mitigating the effects of toxic stress by building buffering protective factors, and preventing the early initiation of substance use in adversity-impacted youth.

The purpose of this paper is to describe the protocol of the Teaching Healthy Regulation in Individuals and Vulnerable Environments (THRIVE) study, which evaluates the efficacy of the GRIT program in a randomized controlled trial (RCT). The active control condition was designed to match the intervention in duration and facilitator contact while avoiding components targeting self-regulation or substance use prevention. This secondary prevention intervention integrates HRV-BF technology within CHW-facilitated health coaching to enhance self-regulation in adversity-impacted adolescent-caregiver dyads. By collecting objective data on biopsychobehavioral indicators of self-regulation and toxic stress, the THRIVE study aims to further our understanding of how interventions like GRIT can mitigate the effects of ACEs and prevent the early initiation of substance use.

## Methods

### Study Design and Study Aims

The THRIVE Study is a two-armed RCT designed to evaluate the effects of GRIT, a psychoeducational health coaching intervention aimed at preventing the early initiation of regular alcohol and cannabis use in adversity-impacted adolescents ages 11 to 14 who are at high risk for toxic stress. This study will include two groups: an intervention group receiving the GRIT intervention and an active control group receiving a digital literacy curriculum. The study will assess the impact of the GRIT intervention on self-regulation and substance use outcomes through repeated measures at pre-intervention, post-intervention (2 months post-baseline), 6-month follow-up (8 months post-baseline), and 12-month follow-up (14 months post-baseline).

There are two specific aims for this study: (1) test the efficacy of GRIT on preventing the early initiation of regular alcohol and cannabis use among adversity-impacted adolescents ages 11–14 years who do not regularly use these substances at baseline; and (2) test the mediating effects of youth and caregiver self-regulation on the relationship between the GRIT program and adolescent substance use outcomes. A digital literacy active control group will allow for comparison in youth and caregiver outcomes. We hypothesize that adolescents who receive GRIT will have lower rates of regular alcohol and cannabis use compared to those in the active control group post-intervention, and that youth and caregiver self-regulation will mediate the relationship between the GRIT intervention and youth outcomes.

### Ethics Approval

Ethics approval was obtained from the University of California, Irvine Institutional Review Board (IRB; #4821). Caregivers provide written informed consent, and adolescents provide assent before participation. Consent and assent are obtained by trained research staff in accordance with IRB approval. Important protocol changes will be submitted to the IRB for approval prior to implementation. Approved changes will be updated to the trial registry. The study poses minimal risk to participants. We do not expect to see any detrimental risks or discomforts arising as a result of this health coaching intervention. Nevertheless, participants may experience emotional or psychosomatic reactions from sensitive information discussed, reported, or described. To ameliorate this, we provide a mental health resource guide at the first in-person assessment. Adolescents may feel a sense of embarrassment about seeking help, and caregivers may feel embarrassment about possibly being perceived as a “bad caregiver” or may feel a sense of stigma regarding the benefits of mental health. To address this, we will instruct the community health workers (CHWs) to validate and normalize healthy help-seeking behaviors, as well as unpack any stigmatizing feelings toward the intervention itself. No financial compensation for trial-related harm or additional post-trial care is anticipated.

### Patient and Public Involvement

The GRIT intervention was developed based on the literature on evidence-based strategies, previous family-based interventions (e.g., STRIVE), and the California Surgeon General’s recommendations. Patients were not involved in the design or conduct of the study, however health sciences students who served as research assistants and health coaches in the pilot study and community health workers assisted with study design and implementation.

### Power and Sample Size

We used the General Linear Mixed Model Power and Sample Size (GLIMMPSE) application to estimate the sample size needed for this study using the approach for longitudinal data (29). We calculated the sample size needed to detect a 40% lower change in use across time among the GRIT versus active control arm for both outcomes, as the Strengthening Families Program cited 50% reductions (30). In addition, we judged that a 40% reduction in initiation rate would be needed for a clinically meaningful effect. Given that exposure to four or more ACEs is associated with a two-to three-fold increase in early initiation (i.e., before age 14) of alcohol and cannabis use and national high school samples report initiation of alcohol before 13 to be 15% and cannabis to 5%, we conservatively assumed a 20% initiation for alcohol and 8% for cannabis for our high-risk study population (31–34). We also accounted for 20% attrition during the 14-month follow-up period and a variance inflation factor of 1.4 to accommodate the mediation analysis. Under these assumptions, a sample size of 105 dyads per arm (total N = 210 dyads) would be needed to provide 80% power at a nominal alpha of 0.025 for each outcome (adjusted for multiplicity to achieve an overall alpha of 0.05 for both outcomes). Previous research, such as the Support to Reunite, Involve, and Value Each Other (STRIVE) study and its adaptation, STRIVE +, has informed the sample size for this study. STRIVE evaluated a 5-session dyadic psychoeducational intervention with youth experiencing homelessness, enrolling 151 youth with a retention rate of 77% at a follow-up (3, 6, and 12 months) (35). STRIVE demonstrated efficacy in significantly reducing substance use, sexual risk, alcohol use, and illicit drug use over 12 months compared to the control condition. Given these findings, family based-interventions like GRIT may similarly reduce substance use and improve overall health and well-being. The findings from STRIVE+ further informed the design of our study, particularly highlighting the need for additional sessions and booster sessions. In STRIVE+, parents requested more sessions to practice newly acquired skills, as they experienced difficulties with familial connection. Based on STRIVE’s successful retention and outcomes, we believe that a sample size of 210 dyads (N=420) for the GRIT study is reasonable, as it allows us to detect meaningful differences in substance use outcomes between the GRIT intervention and the control group.

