
### Sampling

Two hundred and ten adolescent-caregiver dyads (N=420), with adversity-impacted youth aged 11–14, will be recruited. Adolescents are considered adversity-impacted if they score in the high-risk category (4 or more ACEs or any number of ACEs and an ACE-related condition [e.g., school difficulties, symptoms of anxiety and/or depression]). Youth will be recruited from schools, health clinics, and youth-serving community organizations in Southern California. Eligible participants will be randomly assigned to either the GRIT intervention or the active control intervention (i.e., Digital Literacy).

Inclusion criteria for youth include: 1) being aged 11–14 years and scoring in the high-risk category on the ACEs and Toxic Stress Risk Assessment Algorithm; 2) having access to a smartphone and willingness to download an app if randomized to the GRIT intervention; and 3) have a positive, supportive adult such as a parent/guardian/primary caregiver aged 18 years or older who is English or Spanish-speaking and willing to participate in the intervention. The inclusion criteria for caregivers require them to be willing to engage in the intervention alongside the youth participant.

Exclusion criteria for youth participants include: 1) reporting alcohol or cannabis use within the last 14 days; 2) currently being enrolled in another family-based intervention (e.g., family therapy); 3) being in acute distress and requiring immediate care (e.g., imminent risk of harm to self or others, active psychosis); 4) requiring supervised visits by the Department of Children and Family Services (DCFS) with the identified caregiver; and 5) cases where the parent/guardian/primary caregiver declines participation, in which case the family will referred to other community-based programs.

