### Outcomes

The primary outcome is adolescent initiation of regular alcohol and cannabis use. Alcohol and cannabis use will be measured using items from the CDC Youth Risk Behavior Survey (YRBS) and the frequency of use will be assessed using the Timeline Followback (TLFB) method. Regular alcohol or cannabis use is defined as at least weekly use. Secondary outcomes include anthropometrics, heart rate variability, emotional regulation, psychological health, health behaviors, and family functioning. Outcomes will be measured at baseline, post-intervention (2 months), 6 months post-intervention, and 12 months post-intervention.

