### Data Analysis Plan

Baseline characteristics will be summarized using descriptive statistics to assess group balance. Primary analyses will follow the intention-to-treat principle, with all randomized participants included. Changes in adolescent alcohol and cannabis use will be compared between study arms using generalized linear mixed models (GLMMs) to account for within-subject correlation over time. Alcohol and cannabis use will be dichotomized as no or occasional use versus regular use (weekly or more) to evaluate the intervention’s effect on preventing initiation of regular substance use. Statistical significance will be assessed using two-sided tests with an alpha level of 0.05.

Multilevel mediation analyses will be conducted to examine mechanisms underlying intervention effects, with youth and caregiver emotional regulation specified as primary mediators. Additional exploratory mediators will include heart rate variability, psychological and cognitive flexibility, youth health behaviors (HRV biofeedback practice, sleep, nutrition, physical activity), and environmental factors (parental monitoring, family functioning, and caregiver substance use). Indirect and direct effects will be estimated using residual-based bootstrap methods to generate 95% confidence intervals. Sex differences will be evaluated in secondary analyses by including a sex-by-intervention interaction term.

Our primary analysis will be performed using mixed effects analysis, which provides unbiased estimates when missing data is missing at random (MAR). We will also consider multiple imputations to handle missingness using the Rubin method implemented in R package mice (53,54).

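### The sample size is planned on rates of initiation, but the primary outcome counts only weekly-or-more use, so the stated 80% power does not apply to the outcome that will be analysed

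*Protocol article*

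**What the plan says.** **Planning rates (Protocol article, Power and Sample Size).** The starting point and the alcohol rate stand in one sentence: "national high school samples report initiation of alcohol before 13 to be 15% and cannabis to 5%, we conservatively assumed a 20% initiation" for alcohol, followed by 8% for cannabis. The uplift rests on the statement that "exposure to four or more ACEs is associated with a two-to three-fold increase in early initiation (i.e., before age 14"). The target is a 40% reduction, with 20% attrition over 14 months, a variance inflation factor of 1.4, and 80% power at alpha 0.025 per outcome. This gives 105 dyads per arm.

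**Primary outcome (Outcomes; Data Analysis Plan).** The outcome is initiation of regular alcohol and cannabis use: "Regular alcohol or cannabis use is defined as at least weekly use". For the mixed model, use is "dichotomized as no or occasional use versus regular use (weekly or more").

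**Population and window (Study Design and Study Aims; Sampling).** Participants are aged 11 to 14, are not regular users at baseline and are followed to 14 months after baseline. Use in the last 14 days is an exclusion; earlier use is not. Eligibility is "4 or more ACEs or any number of ACEs and an ACE-related condition".

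**Abstract.** The aim is given there as efficacy "in delaying the initiation of alcohol and cannabis use", without the word regular.

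**The concern.** The planning rate and the outcome are on different scales. A young person who starts drinking occasionally belongs in an initiation rate of 20%, but is a non-event in the primary analysis. The source figure also accumulates up to an age, whereas the trial counts new weekly use in a 14-month window. The article takes no step from one to the other.

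The power statement is the formal justification for 210 dyads. If weekly use turns out to be uncommon at this age, the primary comparison would rest on a handful of events per arm. Intervals would be wide, the binary mixed model might be unstable, and a null result could be misread as evidence of no effect.

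**Working it through.** **1. Do the two definitions match?**

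| | Planning rate | Primary outcome |
|---|---|---|
| Behaviour | Initiation | At least weekly use |
| Occasional use | Not separated out | Non-event |
| Window | Before age 13 (source); before age 14 (multiplier) | 14 months from baseline |
| Starting population | National high-school samples, uplifted for ACEs | Ages 11 to 14, not regular users at baseline |

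In the same youth over the same period, weekly users are a subset of users, so on this element the planning rate cannot be too low. How much too high it is cannot be read from the article.

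**2. What does *conservatively* cover?** A full two- to three-fold uplift would give 2 × 15% = 30% to 3 × 15% = 45% for alcohol, and 2 × 5% = 10% to 3 × 5% = 15% for cannabis. The plan uses 20/15 = 1.33-fold and 8/5 = 1.6-fold. The caution is real, but it is on the initiation scale.

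**3. Inputs for the range.**
- Completers per arm: 105 × (1 − 0.20) = 84.
- GRIT rate: p2 = 0.6 × p1 (40% reduction).
- Alpha 0.025 per outcome (Power and Sample Size), two-sided tests (Data Analysis Plan): z = 2.241.
- The variance inflation factor is not applied, which favours the plan.
- Control rates p1 of weekly use: **assumed** at 10%, 5% and 2%, because the article gives none.

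**4. Formula.** With p̄ = (p1 + p2)/2, s0 = √[2p̄(1 − p̄)/84] and s1 = √{[p1(1 − p1) + p2(1 − p2)]/84},

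power = Φ[(p1 − p2 − 2.241·s0)/s1] + Φ[(−(p1 − p2) − 2.241·s0)/s1].

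**5. The plan's own figure first.**
- Alcohol, 20% vs 12%: s0 = 0.0566, s1 = 0.0562. The first term is Φ[(0.08 − 0.1268)/0.0562] = Φ(−0.83) = 0.20 and the second is negligible. Power is about 20%, with 84 × 0.20 = 16.8 vs 84 × 0.12 = 10.1 events.
- Cannabis, 8% vs 4.8%: power about 8%, with 6.7 vs 4.0 events.

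This test does not reproduce 80% power. For 80% it needs 398 per arm for alcohol and 1,111 for cannabis before any inflation. The plan used GLIMMPSE for longitudinal data and does not give the correlation or variance inputs, so its run cannot be repeated. That shortfall is a separate sample-size question, and the present point does not depend on it.

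**6. The range for weekly use.**

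| Assumed control rate | GRIT rate | Expected events, control vs GRIT | Power |
|---|---|---|---|
| 10% | 6% | 8.4 vs 5.0 | 9.9% |
| 5% | 3% | 4.2 vs 2.5 | 5.9% |
| 2% | 1.2% | 1.7 vs 1.0 | 3.8% |

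Example at 10%: s0 = 0.0419, s1 = 0.0418. The first term is Φ[(0.04 − 0.0938)/0.0418] = Φ(−1.29) = 0.099, and the second adds less than 0.001.

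**The case against.** The strongest reply is that the protocol was cautious. The rates of 20% and 8% sit well below a full two- to three-fold uplift, and that discount leaves room for youth with 1 to 3 ACEs. As an illustration, suppose youth with four or more ACEs start at twice the cited rate and the others at the cited rate. Then 15% × (1 + f) = 20% needs only f = one third of the sample to have four or more ACEs, and 5% × (1 + f) = 8% needs f = 60%. This stands: the mixed ACE eligibility does not by itself make the rates too high, and *conservatively* is defensible for initiation. It does not answer the difference between initiation and weekly use.

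Four stronger readings are tempting, and the documents do not support them.
- *Every difference pushes the planned rate too high.* Participants enter at 11 to 14 and are followed for 14 months, so many are observed after age 13, when the source window has closed. The baseline exclusion covers only the last 14 days, so earlier users may enter and progress. Only the step from initiation to weekly use has a certain direction.
- *The planned outcome is far commoner than weekly use.* No weekly-use rate is given and the cited sources are not shown. Even reading initiation as lifetime first use of any amount is an interpretation, although nothing in the text says weekly or regular.
- *The low power in the table is all due to the mismatch.* The same test gives only about 20% and 8% at the planned rates, and it is a single-time comparison rather than the planned longitudinal analysis.
- *Analysing any use would rescue the trial.* By this test it would not be well powered either, and 20% and 8% are not 14-month rates of any use.

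The abstract's wording is a condensation and a minor point, since the aims, outcomes and analysis sections all specify regular use.

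**Conclusion.** The point holds and the text is wrong as written: the stated 80% power is calculated for initiation and attached to an outcome of weekly-or-more use, with nothing in the article bridging the two. That conclusion rests on the article's own definitions and needs no outside figure.

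The size of the gap is less certain. Across assumed control rates of 10% down to 2%, expected events in the control arm fall from about 8 to about 2, and power from about 10% to 4%. These figures assume 84 completers per arm, a 40% reduction, two-sided alpha 0.025, a simple two-proportion test and no variance inflation. They show how sensitive the plan is to the missing rate; they do not estimate the trial's actual power.

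**What to change.** 1. In Power and Sample Size, state and justify a 14-month control-arm rate of weekly-or-more use, separately for alcohol and cannabis, in youth not using regularly at baseline. Give expected events per arm and restate power across a plausible range of those rates.
2. Limit *conservatively* to the initiation scale, where it is justified by the modest uplift.
3. Optionally, add initiation of any alcohol use and of any cannabis use among baseline never-users as a new prespecified secondary outcome. The Substance Use section already collects history and age of onset through the YRBS items. It is not among the listed secondary outcomes, so this is an addition. It needs its own 14-month rate and power statement, without presenting 20% and 8% as that rate and without claiming adequate power.
4. Use the term regular use in the abstract.

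The cost is text and planning figures, with no new data collection. The stated power is likely to fall.

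### The stated 80% power for each primary outcome is not supported by the plan's own assumptions: compared as two proportions, they give about 15–25% for alcohol and 6–10% for cannabis.

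*Protocol article*

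**What the plan says.** All the planning figures stand in the protocol article, section Power and Sample Size.

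- Tool: "We used the General Linear Mixed Model Power and Sample Size (GLIMMPSE) application", in its longitudinal form.
- Target: to "detect a 40% lower change in use across time among the GRIT versus active control arm for both outcomes". The section adds: "we judged that a 40% reduction in initiation rate would be needed for a clinically meaningful effect".
- Control-arm rates: "we conservatively assumed a 20% initiation for alcohol and 8% for cannabis for our high-risk study population".
- Losses and inflation: the authors "accounted for 20% attrition during the 14-month follow-up period and a variance inflation factor of 1.4". The factor is described as "a variance inflation factor of 1.4 to accommodate the mediation analysis".
- Result: "a sample size of 105 dyads per arm (total N = 210 dyads) would be needed to provide 80% power". The significance level behind this is 0.025 per outcome.

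The section closes by calling 210 dyads reasonable because that number can detect meaningful differences in substance use.

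Three other sections matter. The Data Analysis Plan dichotomises use as regular (weekly or more) versus none or occasional, fits generalized linear mixed models, and tests two-sided. Outcomes defines regular use as at least weekly. Sampling excludes youth who report alcohol or cannabis use in the last 14 days.

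**The concern.** A 40% relative reduction from 20% or 8% is a small absolute difference: 8 and 3.2 percentage points. With 84 dyads per arm, the expected counts are about 17 vs 10 for alcohol (84 × 0.20 and 84 × 0.12) and about 7 vs 4 for cannabis (84 × 0.08 and 84 × 0.048). Counts of that size do not normally carry 80% power at alpha 0.025.

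It is also odd that one sample size should serve both outcomes at the same relative reduction, when one is two and a half times as common as the other.

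The authors set 40% as the smallest clinically meaningful reduction. If power at that reduction is far below 80%, the sample size rationale fails for both primary outcomes, and readers will not know how little a non-significant result would say.

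**Working it through.** **Inputs.** From Power and Sample Size: p1 = 0.20 (alcohol) or 0.08 (cannabis); p2 = 0.6 × p1 = 0.12 or 0.048; alpha 0.025 per outcome; 105 per arm; 20% attrition; factor 1.4. From the Data Analysis Plan: two-sided tests and a binary endpoint. So z(0.9875) = 2.2414 and z(0.80) = 0.8416.

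**Sample sizes.** 105 × 0.8 = 84 evaluable per arm; 84 / 1.4 = 60 effective per arm.

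**Attempt to reproduce the plan's figure.** Required n per arm, with p̄ the mean of p1 and p2:

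n = [2.2414·√(2p̄(1−p̄)) + 0.8416·√(p1(1−p1) + p2(1−p2))]² / (p1−p2)²

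- Alcohol: [2.2414·√0.2688 + 0.8416·√0.2656]² / 0.08² = 398 evaluable. After attrition 398 / 0.8 = 498; with the 1.4 factor as well, 697.
- Cannabis: [2.2414·√0.1198 + 0.8416·√0.1193]² / 0.032² = 1,111 evaluable; then 1,389 and 1,945.

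Neither is near 105, and 1,111 / 398 = 2.8, so one n cannot give 80% for both.

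**Power at the planned size.** Power ≈ Φ[((p1−p2) − 2.2414·s0) / s1], with s0 = √(2p̄(1−p̄)/n) and s1 = √((p1(1−p1) + p2(1−p2))/n). For alcohol at n = 84: (0.08 − 2.2414 × 0.05657) / 0.05623 = −0.832, so power is 20%.

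| n per arm | Alcohol | Cannabis |
|---|---|---|
| 105 (no losses) | 25% | 10% |
| 84 (after attrition) | 20% | 8% |
| 60 (attrition and 1.4) | 15% | 6.5% |

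At two-sided 0.05, the level named in the Data Analysis Plan, 84 per arm gives 29% and 13%. A log-rank approximation at 84 per arm and alpha 0.025 gives 21% and 8%. A simulation in which initiation accumulates over the three follow-ups and is never reversed gives 17–20% and 6–7%.

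**Detectable difference at 84 per arm.** For alcohol, 20% vs about 4.5%, a reduction of (20 − 4.5)/20 = 77.5%. For cannabis, no use at all in the GRIT arm still gives only about 66% power.

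**What the longitudinal tool could return.** Take a Gaussian model with constant variance σ² equal to the mean binomial variance of the two arms (0.1328 alcohol, 0.0596 cannabis), equal within-person correlation ρ, and the full difference δ at all three follow-ups. The mean follow-up minus baseline has variance (4/3)σ²(1−ρ). Setting power to 80% with n = 84:

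1 − ρ = δ²·n / [(8/3)·σ²·(2.2414 + 0.8416)²]

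- Alcohol: 0.0064 × 84 / (2.667 × 0.1328 × 9.505) = 0.160, so ρ = 0.84.
- Cannabis: 0.001024 × 84 / (2.667 × 0.0596 × 9.505) = 0.057, so ρ = 0.94.

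The exact F test gives 0.843 and 0.944, so roughly 0.85 and 0.95. Other time patterns and contrasts at 84 per arm need 0.84–0.95 (alcohol) and 0.94–0.98 (cannabis).

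**Are those correlations credible?** A youth with no use in the last 14 days cannot be a weekly user at entry. Baseline regular use is therefore near zero in everyone, and a near-constant baseline cannot correlate with later use or remove variance from it. What remains is the comparison of follow-up visits. Averaging three of them at 84 per arm, each carrying the full difference, gives 50% to 25% (alcohol) and 18% to 10% (cannabis) as correlation rises from 0.1 to 0.7.

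**The case against.** The strongest defence is that the trial was powered on a change over time in a longitudinal mixed model, not on two proportions. For such a contrast, higher within-person correlation raises power, so treating the follow-ups as independent is not an upper limit. This is correct. A reader might infer that repeated measures could never bring the design to 80%. The documents do not support that: the calculation above reaches 80% once the correlation is high enough. What fails is the plausibility of that correlation for this endpoint and these entry criteria.

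Second, the article condenses a fuller protocol, so the missing correlation, variance and time pattern are no fault in themselves. A reader might conclude that the authors' software run contained an arithmetic mistake. That cannot be shown, because the run cannot be repeated. The point is only that the published conclusion does not fit the published assumptions under any plausible completion of them.

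Third, the 1.4 factor is tied to the mediation analysis and may not apply to the primary comparison. This stands, and is why a range is given.

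Fourth, a two-proportion test is not the planned model, and 20% and 8% are initiation rates rather than rates of weekly use. Both stand. The figures here show the scale of the gap; they are not the trial's final power.

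**Conclusion.** The statement of 80% power for each outcome is not supported as written and must be changed. On the plan's rates and effect, a two-proportion comparison at two-sided 0.025 has about 15–25% power for alcohol and 6–10% for cannabis. The bounds correspond to 60 and 105 per arm, with 20% and 8% at the 84 who remain after attrition.

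This rests on three assumptions: the 40% reduction applies to the stated initiation rates; the comparison behaves roughly like one of two proportions; and baseline regular use is close to zero, as the 14-day exclusion implies. If weekly use is rarer than any initiation, as is likely, power for the same relative reduction is lower still.

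The gap is too large to come from the choice of test or rounding. Using alpha 0.05 does not close it. It may be tempting to add that a null result will be read as proof that GRIT fails. No section says so, and the point does not need it.

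**What to change.** Keep 210 dyads and rewrite the power statement.

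1. Replace the 80% claim with power and detectable differences simulated from the binary generalized linear mixed model of the Data Analysis Plan. Use two-sided alpha 0.025 per outcome and 20% attrition, and state the assumed correlation, variance and time pattern.
2. Base the simulation on expected rates of at least weekly use, the analysed endpoint, instead of rates of any initiation.
3. Say whether the 1.4 factor applies to the primary comparison or only to mediation.
4. Until the simulation is done, give the approximate ranges of 15–25% (alcohol) and 6–10% (cannabis), labelled as two-proportion approximations, with a detectable alcohol difference of about 20% vs 4.5% at 84 per arm.
5. Remove or qualify the closing sentence that 210 dyads can detect meaningful differences.

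The cost is one simulation, some rewording and a less favourable stated power. No further participants are required.
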